### Outcomes

Feasibility will be primarily assessed in terms of participant adherence, engagement, and retention. Adherence will be evaluated by tracking participant attendance and the number and proportion of intervention sessions completed, with reasons for nonadherence recorded to determine whether these are related to the intervention or other factors. Engagement will be assessed by documenting completion of each component of the intervention, including participation in music therapy activities and any prescribed between-session practice, alongside interventionist ratings of participant engagement and proficiency where applicable. Participants will also be asked to provide brief open-ended feedback regarding their ability to engage with the intervention and any difficulties encountered. Retention will be assessed by recording the number and proportion of participants who withdraw from the study and those who complete the final assessment, with reasons for dropout documented. These measures will be used to determine whether the intervention can be delivered as intended, identify barriers to participation, and establish whether adherence and retention rates support progression to a larger definitive trial.

At baseline, participants complete an intake interview wherein demographic information including personal background and role within the university is recorded, as well as relevant information relating to participants’ general physical and mental health, experience of pleasure in daily life, any specific loss of pleasure in music, pleasure in preferred activities and lifestyle, and their historical and current relationship to music and music activity. A descriptive baseline of participants’ current level of hedonic capacity, including current experience of pleasure, enjoyment, social engagement, motivation, and decision-making capacity, is also recorded. These topics are revisited in a postintervention exit interview to capture perceived changes in pleasure experience and lifestyle associated with increased hedonic capacity; participant experience and characterization of musical pleasure through the intervention process; and participant experience of the intervention. Interview transcripts are generated for qualitative analysis. For interview questions, refer to Multimedia Appendix 1.

Pre-post DARS scores are recorded during the screening survey and prior to the exit interview. This timing allows the scale to be used to determine participant eligibility for the study. Pre-post SHAPS scores are recorded on fMRI scanning days, as part of the prescan briefing process. This timing provides an indicator of hedonic capacity at the time of scanning. Pre-post score comparisons from these validated tools will also be used to assess changes in anhedonia severity in individual participants after the intervention.

Scanning sessions for fMRI data collection will be conducted on a 7T MAGNETOM Plus MRI system (Siemens Healthineers) located at the Melbourne Brain Centre Imaging Unit (MBCIU) at the University of Melbourne. Imaging will consist of (1) a structural scan, (2) resting-state fMRI, and (3) BOLD fMRI, using 4 tasks: reward reversal, music, naturalistic positive music, and naturalistic neutral music listening. These tasks have been specifically developed to target reward- and music-processing–related neurocircuitry, which are hypothesized to be relevant to our intervention.

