### Eligibility Criteria

To identify participants with anhedonia, communications included a link to an online screening survey that prospective participants could independently access, comprising the DARS and questions assessing the inclusion criteria. The research team reviewed all survey responses, and eligible prospective participants were identified as scoring <44 on the DARS [45], based on the group differences identified between patients with major depressive episodes and healthy controls. This score has also been used in a study of university students where none of the healthy controls scored <44 points on the total scale [52]. All participants were required to complete a magnetic resonance imaging (MRI) safety implant checklist and be screened by qualified radiographers to deem them compatible with an MRI scan.

The inclusion criteria are being a professional, research, or academic member of the university community, having the cognitive capacity to select and discuss pleasure-inducing music, being aged >18 years, scoring <44 on DARS, agreeing to participate and having the capacity to provide informed consent, having a self-identified interest in music, and having English literacy skills suitable for participation in interviews. Exclusion criteria for all groups are failure to meet scanning requirements, including having metallic objects in the body (eg, a cardiac pacemaker or cochlear implant), a history of claustrophobia, permanent metal dental appliances, or a body weight ≥120 kg, or having a diagnosis of schizophrenia or MDD.

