### Participant Timeline

The schedule for data collection is outlined in Figure 1. The DARS is independently completed online by participants who volunteer to participate. Questions on the online platform also confirm that they are professional, research, or academic members of the university community, aged >18 years, do not have a diagnosis of schizophrenia or MDD, and are interested in music. If these questions are confirmed and their score is <44 on the DARS, they are contacted by the research team to complete an intake interview, where this information is confirmed along with their English literacy skills, reflective cognitive capacity, and understanding of the requirements of the study. Times are then scheduled at the study center for further preintervention testing, including completion of the SHAPS and fMRI data acquisition. Brief interviews are conducted following the data acquisition to identify any feasibility issues with the music task. Following scans, participants commence 4 months of weekly meetings with the interventionist and undertake the daily music activities. Following completion of the intervention, participants return to the study center to complete the posttest measures of the DARS, SHAPS, and fMRI data acquisition and then participate in an exit interview.

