### Data Analysis

Repeated-measures *t* tests will be conducted on pre-post DARS and SHAPS scores to examine directional change. Hedges *g* will be calculated to estimate effect sizes, which will inform power calculations for a future fully powered study. *P* values will be reported descriptively but not interpreted as indicators of statistical significance, given the small sample size (N=13).

fMRI data will be analyzed using individual general linear models to identify longitudinal changes associated with the intervention. For each task, blocked-design general linear model analyses will be specified at an individual participant level in Statistical Parametric Mapping version 12 (SPM12) to model specific conditions of interest. For the reward-reversal task, this will involve contrasting unexpected punishment trials with expected reward trials. For the music task, the primary contrast will compare pleasurable music with neutral music. Repeated-measures, flexible factorial designs (within-subject factors: primary contrast×time) will be used at the group level to examine longitudinal changes. These will then inform exploratory investigations of associations between these effects and symptom improvement.

Inductive thematic analysis will be used to identify patterns in descriptions of change and group similar ideas from across the interview data [58]. Labels will be selected that verifiably represent the participant quotes contained within each theme, and these will be checked by the research team as a form of peer debriefing to identify blind spots and adjusted when found to be dissimilar.

Sequential analysis will be conducted by comparing the themes from interviews to overall changes in participant scores on psychometric measures of anhedonia from preintervention to postintervention assessments to identify any correspondences. Themes will also be compared to any changes in activity across reward processing regions during reward fMRI tasks and targeted music listening evident from preintervention to postintervention assessments that correspond with patterns of congruence in the psychometric data.

Feasibility will be documented based on verbal feedback following fMRI data acquisition and in the final interview. Anything beyond individual preferences will be used to inform necessary changes to the protocol.

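### The DARS baseline is the screening score that had to be below 44 for entry, so regression to the mean biases the expected pre-post DARS change and its Hedges g towards improvement

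*Protocol article*

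**What the plan says.** In Outcomes, the article places the two DARS readings: "Pre-post DARS scores are recorded during the screening survey and prior to the exit interview". It gives the reason for the first: "This timing allows the scale to be used to determine participant eligibility for the study". Eligibility Criteria sets the threshold: "eligible prospective participants were identified as scoring <44 on the DARS". Low is the worse direction, since the article cites a student study in which "none of the healthy controls scored <44 points on the total scale".

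Participant Timeline describes no further DARS before treatment. After the intake interview it lists "further preintervention testing, including completion of the SHAPS and fMRI data acquisition". The SHAPS is handled differently: "Pre-post SHAPS scores are recorded on fMRI scanning days, as part of the prescan briefing process".

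In Data Analysis, repeated-measures t "tests will be conducted on pre-post DARS and SHAPS scores to examine directional change". The same section says that Hedges g will inform power calculations for a later study and that P values are descriptive only. Limitations names the missing control group and the small sample. It does not mention regression to the mean.

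**The concern.** One reading does two jobs. It admits people because it is low, and it is then the value from which improvement is measured. Any score with test-retest correlation below 1 contains a transient part, and people picked for a low reading will on average have a negative transient part at that moment. It is not expected to persist four months later, so the expected second score is higher with no treatment effect. With no control arm, nothing in the design separates this from benefit.

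Selection also removes the upper part of the baseline distribution. The baseline SD is therefore smaller than among all respondents, and a g divided by it is enlarged a second time. The article does not say which SD will be used.

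What is at stake is mainly planning. Study Design and Data Analysis both send the estimated effect to the sample size of the next study, and an inflated g would make that study too small. DARS change is also what the interview themes are compared with, and the fMRI changes are to be related to changes in anhedonia symptoms, so part of what they are matched against could be artefact.

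**Working it through.** **The plan's own figure.** There is nothing to reproduce. N=13 is justified in Sample Size by qualitative depth and scanning resources. No DARS SD, reliability or effect size is given.

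**Inputs from the article.** Selection on DARS below 44; the same reading as baseline; n=13, so 12 degrees of freedom; paired analysis; no control group.

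**Assumptions, not in the article.** Scores are normal among survey respondents, with equal SD at both times (set to 1). Test-retest correlation over about four months is ρ = 0.7 to 0.9. The cut-off lies c SDs from the respondents' mean, with c from −1 to +1 (16% to 84% of respondents below 44). There is no treatment effect.

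**Formulas.**
- λ = φ(c)/Φ(c), the distance of the selected group's mean below the respondents' mean
- Variance of the selected baseline: v = 1 − cλ − λ²
- Expected change: (1 − ρ)λ
- Variance of change: (1 − ρ)²v + 1 − ρ²
- Hedges correction: J = 1 − 3/(4×12 − 1) = 0.936
- g on baseline SD = J × change/√v; g on SD of change = J × change/√(variance of change)

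**One case in full (c = −0.5, ρ = 0.7).** λ = 0.352/0.309 = 1.141. v = 1 + 0.571 − 1.302 = 0.268, SD 0.518. Expected change = 0.3 × 1.141 = 0.342. Variance of change = 0.09 × 0.268 + 0.51 = 0.534, SD 0.731. g = 0.936 × 0.342/0.518 = 0.62 on the baseline SD, and 0.936 × 0.342/0.731 = 0.44 on the SD of change.

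| c | Share below 44 | ρ | Expected change (SD) | g, baseline SD | g, SD of change |
|---|---|---|---|---|---|
| −1 | 16% | 0.7 | 0.46 | 0.96 | 0.59 |
| −0.5 | 31% | 0.7 | 0.34 | 0.62 | 0.44 |
| 0 | 50% | 0.7 | 0.24 | 0.37 | 0.30 |
| 0 | 50% | 0.9 | 0.08 | 0.12 | 0.17 |
| +0.5 | 69% | 0.7 | 0.15 | 0.21 | 0.19 |
| +1 | 84% | 0.9 | 0.03 | 0.03 | 0.06 |

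The expected change is positive for every ρ below 1 and zero only at ρ = 1. The standardiser matters: at c = −1 and ρ = 0.7 the selected baseline SD is 0.45 of the respondents' SD, which is why g reaches 0.96 there.

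**What an inflated g does to the next trial (illustration).** Suppose the true standardised difference is 0.5 and the planning value is too high by 0.3. A two-arm trial at 80% power, two-sided 0.05, would be sized at 25 per arm instead of 63. Its real power would be about 42%.

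**The case against.** The strongest reply is that this is a feasibility pilot. Feasibility is the primary aim, and Outcomes ties progression to adherence and retention. Sample Size calls the study underpowered for inference, P values are not to be read as significance, and Limitations admits the missing control group. All of this stands and lowers the severity. It does not reach the effect size, which is a planned product of the study and carries the bias. Nor does the admitted lack of a control group cover it, because this source can be reduced within a single arm.

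A second reply is that the size is unknown, and this also stands. Recruitment was aimed at people with anhedonia, so most respondents may have scored below 44. With 69% to 84% eligible, g falls to 0.03 to 0.21 on the baseline SD. The upper end needs both a strict cut-off and a baseline-SD standardiser that the article does not specify.

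Three stronger readings go beyond the documents:
- A reader might infer that the DARS is bound to show benefit. The shift is in expectation only, and 13 observed changes may differ.
- A reader might infer that low screening scores were rewarded, because Ethical Considerations says a novel intervention may have motivated participation. Nothing says respondents knew the cut-off or shaded their answers.
- A reader might infer that the SHAPS should become the lead measure. It was not the selection score, but Study Design reports strong convergence with the DARS, so it can regress in part. The article also prefers the DARS for covering anticipatory as well as consummatory pleasure. Changing the lead after data collection is not clearly better.

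**Conclusion.** The point holds as a bias in expectation, with a certain direction and an uncertain size. The article itself establishes the shared reading, the cut-off on the worse side, the absence of a second baseline DARS and the absence of a control group. The spurious g of about 0.03 to 0.96 (baseline SD) or 0.06 to 0.59 (SD of change) rests on the assumed normality, the correlation of 0.7 to 0.9 and the cut-off position. It ranges from negligible to large, and the article does not show where this study lies. The point should be fixed before the DARS effect size is reported or reused. It does not undermine the feasibility aim.

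**What to change.** Data collection is reported as concluded and analysis as still ahead, so items 1 to 4 concern analysis and reporting and item 5 concerns reuse of the protocol.

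1. Name regression to the mean in Limitations, separately from the missing control group.
2. State the standardiser of Hedges g, and do not use the baseline SD truncated at 44.
3. Beside the raw DARS change, report a range for the expected regression-to-the-mean shift over stated test-retest correlations. "The research team reviewed all survey responses", so the mean and SD of all screening responses should be obtainable. Use them where consent and ethics approval allow, since the article documents consent from participants only. Otherwise use a range of assumed cut-off positions. Present the result as a sensitivity analysis, not a corrected estimate, because the reliability is assumed.
4. Do not size the next trial on the unadjusted DARS g.
5. In the protocol to be reused, repeat the DARS with the SHAPS at the preintervention scan visit, take that reading as baseline, and keep the screening DARS for eligibility only. This removes mainly the short-term part of the bias; slower fluctuation over four months would remain.

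The cost is some wording, one extra calculation and one repeated questionnaire. The reported DARS effect will look less favourable.

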### Sample Size

A sample size of 13 was selected to provide adequate depth of qualitative data (interviews) while maintaining feasibility for resource-intensive fMRI data collection. This sample size is sufficient for exploratory mixed methods analysis and effect size estimation, although it is underpowered for statistical inference [53].

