## Discussion

### Principal Findings

Music therapy has demonstrated feasibility and effectiveness in reducing negative symptoms and/or enhancing quality of life in a range of chronic mental health and physical health conditions. This study outlines a unique protocol for a mixed methods pre-post pilot test that is based on findings from 3 prior case studies using the same intervention, which resulted in improved outcomes among all participants. It aims to investigate whether music therapy reduces anhedonia symptomatology and to explore the interaction between a combination of biophysiological, neuropsychological, and sociobehavioral mechanisms of improvement. Biophysiological mechanisms will be investigated through a comparison of musical pleasure in healthy volunteers and the intervention group. Neuropsychological mechanisms will be investigated using a comparison of preintervention and postintervention test scores on psychometric measures of anhedonia. Sociobehavioral outcomes will be explored through evaluative interviews that probe the importance of the regular therapeutic care and support provided.

No other studies have integrated data to explore the effect of music therapy on anhedonia. Only 1 other study has been identified that reports improvements in anhedonia symptoms, which was based on a similar program that used mindfulness as the key intervention rather than music therapy [8]. We hypothesize that musical pleasure may serve as a gateway to the reactivation of the pleasure system and propose that regular, guided, personally selected pleasure-inducing music activities can promote increased limbic activity, which may be one mechanism through which music therapy reduces anhedonia symptomatology. Currently, this is a 4-month process involving weekly meetings with the guiding therapist and daily engagement with pleasure-inducing music-based activities. This process could be changed and/or made more efficient with different populations once the mechanism is better understood.

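### Individual change is to be assessed from one pre and one post score with no allowance for measurement error, and on the DARS the pre score is the selection score

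*Protocol article*

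**What the plan says.** Under Outcomes, after describing when the two scales are given, the article adds an individual-level use of the scores: "Pre-post score comparisons from these validated tools will also be used to assess changes in anhedonia severity in individual participants after the intervention".

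The timing of the two scales differs.

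- DARS: "Pre-post DARS scores are recorded during the screening survey and prior to the exit interview". The reason given is "This timing allows the scale to be used to determine participant eligibility for the study". Under Eligibility Criteria, "eligible prospective participants were identified as scoring <44 on the DARS". One DARS reading is therefore both the entry score and the baseline.
- SHAPS: "Pre-post SHAPS scores are recorded on fMRI scanning days, as part of the prescan briefing process". It is not an entry criterion, and its baseline is taken after selection.

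Data Analysis handles the same scores with repeated-measures t tests and Hedges g, with P values reported descriptively. These are group quantities. Neither section gives a minimum change, a measurement-error bound or a reliable-change rule for one person. There is no control arm.

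**The concern.** A single pre-post difference in one person carries the error of both readings. Without a bound it cannot be said whether the person changed or the scale fluctuated. The group t test and Hedges g do not answer that question for an individual.

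The DARS has a second problem, which is fixed in the text rather than inferred. People enter because their screening score is low, and some of those scores are low partly through error. When the same reading serves as baseline, the next reading tends to be higher with no treatment effect. With no control arm, nothing in the design shows how much of a person's gain is of this kind.

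At stake is the individual-level description in a 13-person study that also holds an exit interview with each participant. Chance movement could be reported as a change in anhedonia severity.

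**Working it through.** The article states no error rate for individual change, so there is no figure of its own to reproduce. The check asks how often a favourable difference arises when nothing has changed.

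**Inputs from the article:** 13 participants; one pre and one post reading per scale; DARS entry at <44 on the reading that is also the baseline; SHAPS not used for entry.

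**Inputs assumed, because the article does not give them:** reliability r of 0.7, 0.8 or 0.9; the DARS cut-off at the lowest 5%, 10% or 20% of screened scores; normal scores in SD units, with pre and post sharing one true score and having independent errors.

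**SHAPS.** With no selection on the scale, the difference is symmetric about zero, so P(favourable) = 0.5 if ties are ignored. That is 13 × 0.5 = 6.5 people, and the binomial chance of 7 or more of 13 is 0.50. With whole-number scores (assumed SD 5 to 8 points), 6% to 18% of pairs tie and P(favourable) falls to 41% to 47%, or 5.3 to 6.1 of 13.

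**DARS.** Given a baseline x in SD units, the post score has mean r·x and variance 1 − r². Hence P(post > pre | x) = Φ(−x·√((1 − r)/(1 + r))). Averaging over x below the cut-off gives:

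| Entry from lowest | r = 0.7 | r = 0.8 | r = 0.9 |
|---|---|---|---|
| 5% | 80.4% | 75.2% | 68.1% |
| 10% | 76.6% | 71.9% | 65.6% |
| 20% | 71.8% | 67.7% | 62.5% |

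Of 13 people this is 13 × 0.625 = 8.1 to 13 × 0.804 = 10.5. With the cut-off placed anywhere from the mean to 2 SD below it, the range widens to 57% to 84%.

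**Effect of a reliable-change limit.** SEM = SD × √(1 − r), so the limit 1.96 × √2 × SEM equals 1.96 × √(2(1 − r)) SD:

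- r = 0.9: 1.96 × √0.2 = 0.88 SD
- r = 0.8: 1.96 × √0.4 = 1.24 SD
- r = 0.7: 1.96 × √0.6 = 1.52 SD

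With zero true change, 2.5% of participants exceed the limit in the favourable direction on the SHAPS (1.9% to 3.0% with whole-number scores), about 0.3 of 13. On the DARS, under the selection fractions in the table, 4.7% to 10.7% exceed it, or 0.6 to 1.4 of 13. The DARS figure stays above 2.5% because the limit allows for measurement error but does not remove the upward shift caused by selecting on the baseline. That shift averages (1 − r) × φ(c)/Φ(c) SD for a cut-off at −|c|: 0.14 SD at r = 0.9 and the lowest 20%, and 0.62 SD at r = 0.7 and the lowest 5%.

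**The case against.** The strongest reply is that the article nowhere says any favourable difference counts as improvement, and plans no responder classification or count. That is correct. A reader might infer such a rule from an unbounded comparison, or might take the Discussion's description of the study as "based on findings from 3 prior case studies using the same intervention, which resulted in improved outcomes among all participants" as evidence that the rule is already in use. That sentence names no scale and no criterion, and the Introduction says the earlier DARS results were supported by interview data. It does not establish how individuals were judged.

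It is also tempting to say that the study will seek explanations in the interviews of people wrongly labelled as responders. The second research question and Data Analysis set interview themes against overall score changes, and the thematic analysis is not split by individual score change. That stronger harm is not supported.

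Further, the individual reading is secondary in a feasibility pilot that discloses its sample as "although it is underpowered for statistical inference", and an error bound might sit in a fuller document that is not shown. This lowers the weight of the point. It does not remove it, because the article commits to assessing individuals from these scores and itself fixes the DARS baseline as the selection score. A threshold held elsewhere would not undo that selection.

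Lastly, the SHAPS figure of one half holds for any symmetric difference and is slightly too high once ties count, and the DARS figures depend on assumed inputs. Both points stand, which is why the DARS result is given as a range.

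**Conclusion.** The point holds in a limited form. The article will assess change in individuals from one pre and one post score with no allowance for measurement error, and on the DARS it does so from a baseline on which people were selected. If a favourable difference is read as change, zero true change produces it in just under half of participants on the SHAPS and in most participants on the DARS, roughly 62% to 80%.

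The DARS range rests on assumed reliability and on an assumed position of the cut-off among those screened. The direction does not: selecting on a fallible score and reusing it as baseline pushes later differences upward. The SHAPS figure assumes that selection does not carry over to the scan day. If low mood at screening persisted until then and later lifted, the SHAPS would exceed one half as well.

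The documents do not support the claim that the study defines responders by the sign of the difference, or that its individual results cannot carry information. A change larger than the reliable-change limit would still be informative, with the reservation noted for the DARS.

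**What to change.** In Outcomes, add the following beside the sentence on individual participants.

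1. A participant's change on a scale is described as beyond measurement error only if it exceeds 1.96 × √2 × SEM in either direction. The SEM comes from a cited retest reliability and SD for that scale. Any smaller change is reported as no reliable change.
2. Individual-level statements rest on the SHAPS, or on both scales agreeing.
3. The text says that individual DARS gains are inflated because the baseline is the score used for selection, and that the limit does not correct this.

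This takes about a paragraph and uses data already collected. Fewer participants will be described as improved, and the limit depends on reliability estimated in other samples. It should therefore be fixed, with its source, before the scores are examined.
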